### Data management/handling with missing data

Data entries undergo an automatic online check for plausibility and consistency. In case of implausibility, 'warnings' will be produced. A responsible investigator will be obliged either to correct the implausible data or to confirm its authenticity and to give an appropriate explanation. If not corrected, the data will be flagged, enabling a convenient check of all questionable entries. A responsible monitor will check all flagged data and generate questions that are sent back to the responsible investigator. The investigator will resolve all “discrepancies.”

Further checks for plausibility, consistency, and completeness of data will be performed after the completion of the study. Queries will be generated based on these checks, combined with a visual control by a responsible monitor/data manager.

All missing data or inconsistencies will be reported back to the sites and clarified by the responsible investigator. If no further corrections are to be made in the trial database it will be declared closed and used for statistical analysis.

For patients with incomplete follow-up, time to last follow-up date will be used as the censoring time in the analysis of time-to-event data. Missing data of continuous outcomes over time will be handled via the multi-level approach making the implicit assumption that data are missing at random, thus not requiring any direct imputation of missing continuous data. The robustness of this assumption will be explored in sensitivity analyses using pattern mixture models assuming that data are not missing at random. Otherwise, no imputation of missing data will be conducted.

In cases of withdrawal, the reason must be recorded and documented. For patients with incomplete follow-up, time to last follow-up date is used as the censoring time in the analysis of time-to-event data.

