### Outcome measure

#### Primary outcome

The primary outcome will be the change in the score of AHI, SpO2, REM, EEG, ECG, RDI, and ESS from baseline to the end of 1 month of intervention by MAD and CMOA.

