### Statistical analysis

The baseline measures before intervention will be compared with the measures obtained after 1 month and 3 months of intervention. Descriptive and analytical statistics will be done. The data will be presented in mean and standard deviations. The normality of data will be tested by the Shapiro-Wilk test. If the data follows normal distribution parametric tests (Independent sample *t*-test and paired *t*-test) will be used and if the data does not follow normal distribution non-parametric tests (Mann-Whitney *U* test and Wilcoxon signed rank test) will be used. The statistical significance will be set at *p*< 0.05. SPSS (Statistical Package for Social Sciences) Version 20.1 (IBM Corporation, Chicago, USA) will be used as statistical software. The inverse probability censoring weighting (IPCW) approach will be done to estimate a treatment effect in the hypothetical scenario.

We expect to confirm the efficacy of the CMOA in managing moderate OSA against MAD by monitoring AHI, SpO2, REM, EEG, ECG, oro-nasal airflow via a pressure transducer, and ESS before and after 1 month and 3 months.

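### The missing-data section and the statistical analysis section prescribe incompatible analyses for the same continuous outcomes, beside a censoring rule with no outcome and an undefined IPCW analysis

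*Protocol article*

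**What the plan says.** Two sections of the protocol article bear on this point.

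**Data management/handling with missing data** gives three rules for incomplete data:
- For incomplete follow-up, "time to last follow-up date will be used as the censoring time in the analysis of time-to-event data". The rule appears again at the end of the section.
- For continuous measures, "Missing data of continuous outcomes over time will be handled via the multi-level approach making the implicit assumption that data are missing at random". Robustness is to be examined in "sensitivity analyses using pattern mixture models assuming that data are not missing at random".
- Beyond that, "Otherwise, no imputation of missing data will be conducted".

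**Statistical analysis** sets out the comparisons. After a Shapiro-Wilk check it states "If the data follows normal distribution parametric tests" (independent-sample and paired t-tests) will be used, and otherwise Mann-Whitney and Wilcoxon signed-rank tests. It then adds: "The inverse probability censoring weighting (IPCW) approach will be done to estimate a treatment effect in the hypothetical scenario". It names no multi-level model.

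The outcomes are defined under Outcome measure: "The primary outcome will be the change in the score of AHI, SpO2, REM, EEG, ECG, RDI, and ESS from baseline to the end", where the end point in time is the 1-month visit. The secondary outcomes are the same measures at 3 months and at 1 and 3 months.

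**The concern.** A missing-at-random statement is a property of a particular model fitted to the data. It protects a likelihood-based model for repeated measures because that model uses a patient's earlier values when a later one is missing. A t-test or rank test at a single visit makes no such use of earlier values. A reader of the missing-data section would believe dropout is handled under missing at random. A reader of the Statistical analysis section would run tests that do not handle it in that way. Both cannot be the main between-arm analysis of the same measure.

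Two things are at stake. First, if patients doing badly at 1 month are less likely to be seen at 3 months, the two analyses can give different 3-month answers. Second, with several candidate methods and none designated as the main one, the choice could be made after the data are seen.

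**Working it through.** **1. Methods set against outcomes.**

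| Stated rule | Section | What it needs | Is that in the document? |
|---|---|---|---|
| Censor at last follow-up | Missing data (twice) | A time-to-event outcome | No: every outcome is a change in a measurement at fixed visits |
| Multi-level model, missing at random | Missing data | A repeated-measures model in the analysis section | No: only t-tests or rank tests are named |
| Pattern-mixture sensitivity analysis | Missing data | A main model to depart from | Not named in the analysis section |
| IPCW for a hypothetical scenario | Statistical analysis | A censoring event, a scenario and a weighted outcome model | None is given |
| t-tests or rank tests, no imputation | Statistical analysis | Values observed at the visit tested | Yes, which makes them available-case by visit |

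The multi-level model suits continuous measures taken at baseline, 1 month and 3 months. Its conflict is with the named tests.

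**2. Room for loss.** Study design gives a minimum of 16 per group and plans 20. The margin is (20 − 16)/20 = 20%, or 4 per arm. The article does not present this as a predicted dropout rate; it is used here only to set a scale.

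**3. Illustrative shift at 3 months.** Assumptions, none from the document: 1-month and 3-month AHI are jointly normal and standardised, with correlation r of 0.6 to 0.8; the worst 20% by 1-month AHI in one arm have no 3-month value; nobody is selectively lost from the other arm.

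- Cut-off: the 80th percentile of the standard normal, z = 0.8416, with density φ(z) = 0.2800.
- Mean 1-month AHI of those retained: −φ(z)/0.80 = −0.2800/0.80 = −0.350 SD.
- Shift in the observed 3-month mean: r × (−0.350), so 0.6 × (−0.350) = −0.21 SD and 0.8 × (−0.350) = −0.28 SD. Lower AHI is better, so that arm looks better than it is.
- With exactly 16 of 20 kept, the mean of the 16 lowest of 20 normal values is −0.332, giving −0.20 to −0.27 SD.

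**4. Milder selection.** If 20% are lost on average, with the log-odds of loss rising by 0.5 to 1.0 per SD of 1-month AHI (assumed), the retained 1-month mean is −0.096 to −0.173 SD. Multiplying by r gives about −0.06 (0.6 × 0.096) to −0.14 SD (0.8 × 0.173).

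**5. Which analysis removes the shift.** In steps 3 and 4 loss depends only on an observed 1-month value, so the data are missing at random. A correctly specified repeated-measures model recovers the 3-month mean; a 3-month t-test does not. The 1-month comparison is made before anyone is lost, so its bias in these scenarios is zero.

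**6. Scale.** The article gives no effect size or SD for the minimum of 16, so that figure cannot be reproduced. Solving backwards (two-sided 5% assumed, 80% power, normal approximation): (1.960 + 0.842) × √(2/16) = 0.99 SD. If the SD scales are comparable, 0.21 to 0.28 SD is about a fifth to just over a quarter of the implied design effect (0.21/0.99 = 0.21; 0.28/0.99 = 0.28).

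**The case against.** The strongest reply is that an article condenses a fuller plan, and that a statistical analysis plan could say how the multi-level model and the tests relate. For IPCW this has some force, since an undefined scenario is close to detail that such a plan might supply. It does not rescue the rest. The two sections state different analyses of the same measures, and a later document cannot follow both without correcting one.

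Other parts of the reply stand and limit the point:
- The censoring rule is conditional on a time-to-event analysis. With none, it is inert and biases nothing.
- The shift in the working is a deliberately severe, one-sided scenario for a secondary contrast.
- A mixed model with baseline as a covariate gains little at 1 month. A patient with no post-baseline value contributes nothing to it, just as with a t-test. It helps at 1 month only for those who miss that visit but attend at 3 months.
- Stopping the appliance is not the same as missing a visit, and nothing says that patients who stop go unassessed.

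Three stronger readings are tempting, and the document does not support them:
- A reader might infer that the trial will in effect be analysed on complete cases. The article does not say so. Which analysis will be run is undetermined, and the named tests would be available-case by visit, so a missed 3-month visit removes nobody from the 1-month comparison.
- A reader might infer that IPCW cannot apply without a time-to-event outcome. Such weights are also used for dropout in repeated continuous measures; the fault here is lack of definition.
- A reader might infer that the primary result is biased. In the scenario worked through, it is not.

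**Conclusion.** The point holds as a contradiction between two stated rules. The missing-at-random claim belongs to a model that the analysis section never names, and the tests it does name cannot carry that claim. The censoring rule has nothing to apply to, and IPCW cannot be carried out as described.

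The numerical consequence falls mainly on the 3-month secondary contrast: about 0.2 to 0.3 SD under severe one-arm selection, and about 0.06 to 0.14 SD under the milder selection assumed. These figures rest on assumed correlations, an assumed 20% loss and selection on observed 1-month AHI; none is a prediction for this trial. The conflict between the sections does not depend on any of them.

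**What to change.** In the Statistical analysis section:
- Name one linear mixed model for repeated measures as the between-arm analysis of the continuous outcomes (for example AHI, the SpO2 measures, REM-AHI, RDI and ESS). Include arm, visit, arm-by-visit and baseline value, and analyse all randomised patients in their assigned arm.
- Read the 1-month contrast as primary and the 3-month contrast as secondary.
- Keep the rank-based tests as a sensitivity analysis, since the present plan provides for non-normal data.
- State a suitable separate method for the EEG and ECG pattern outcomes, which a linear model does not obviously fit.
- Either delete IPCW or define its censoring event and its hypothetical scenario.

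In the missing-data section:
- Delete both time-to-event censoring sentences.
- Keep the pattern-mixture analysis, stated as a sensitivity analysis of the mixed model.

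The model uses data already scheduled for collection. The cost is a little more analysis work and, because the main test changes, a documented amendment through the route in the Protocol amendments section before the data are analysed.

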### Auditing the data

The investigators agree to allow the auditors/inspectors/monitors to have direct access to the trial records for review, being understood that this personnel is bound by professional secrecy, and as such will not disclose any personal identity or personal medical information. The investigator will make every effort to help with the performance of the audits and inspections, giving access to all necessary facilities, data, and documents.

### Statistical analysis

The baseline measures before intervention will be compared with the measures obtained after 1 month and 3 months of intervention. Descriptive and analytical statistics will be done. The data will be presented in mean and standard deviations. The normality of data will be tested by the Shapiro-Wilk test. If the data follows normal distribution parametric tests (Independent sample *t*-test and paired *t*-test) will be used and if the data does not follow normal distribution non-parametric tests (Mann-Whitney *U* test and Wilcoxon signed rank test) will be used. The statistical significance will be set at *p*< 0.05. SPSS (Statistical Package for Social Sciences) Version 20.1 (IBM Corporation, Chicago, USA) will be used as statistical software. The inverse probability censoring weighting (IPCW) approach will be done to estimate a treatment effect in the hypothetical scenario.

We expect to confirm the efficacy of the CMOA in managing moderate OSA against MAD by monitoring AHI, SpO2, REM, EEG, ECG, oro-nasal airflow via a pressure transducer, and ESS before and after 1 month and 3 months.

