**Methods:**

A prospective interventional study with a randomized controlled trial will be carried out involving 40 participants (sample size), with an apnea-hypopnea index (AHI) > 15–30, recorded on polysomnography (PSG). Study participants will be randomly divided into the following treatment groups: control group or group subjected to mandibular advancement device (MAD, *n*=20) and second group subjected to customized maxillary oral appliance (CMOA, *n*=20). Baseline assessment of apnea/hypopnea index (AHI), oxygen saturation in blood, percentage of rapid eye movement, electroencephalogram, electrocardiogram, oro-nasal airflow via a pressure transducer, and Epworth Sleepiness Scale will be done. Then both study group participants will receive their respective appliances. And after one month and three months of delivery of the appliance, all the parameters, i.e., AHI, oxygen saturation in blood, percentage of rapid eye movement, electroencephalogram, electrocardiogram, oro-nasal airflow via a pressure transducer, and Epworth Sleepiness Scale will be re-evaluated and compared with the baseline measurements. Descriptive and analytical statistics will be done. SPSS (Statistical Package for Social Sciences) Version 20.1 will be used as statistical software. The statistical significance between the two groups after one month and three months will be evaluated at *p*< 0.05.

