**Assessments:**				
Primary outcome			X	
Secondary outcomes				X

The study involves 40 sample sizes. At 80% power of the study, the minimum sample size calculated for each group is 16. However, 20 samples in each group will be selected to minimize errors and to cover any loss of cases during follow-up.

These 40 participants will be randomized by creating a computer-generated randomization list. Participants will be assigned random numbers based on consecutive enrolment into group 1 or a control group subjected to MAD (*n*=20) and another group, i.e., group 2 subjected to CMOA.

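### The Statistical analysis section never names the CMOA-versus-MAD contrast as the efficacy test: it lists within-arm and between-arm tests together, unadjusted for baseline and chosen by Shapiro-Wilk

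*Protocol article*

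**What the plan says.** All places are in the protocol article.

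- Statistical analysis begins with the before-after comparison: "The baseline measures before intervention will be compared with the measures obtained after 1 month and 3 months of intervention". It then provides that, for normal data, "parametric tests (Independent sample *t*-test and paired *t*-test) will be used", and otherwise Mann-Whitney and Wilcoxon signed rank tests. The choice rests on a pre-test: "The normality of data will be tested by the Shapiro-Wilk test". Results are to be given as means and SDs.
- The same section closes with "We expect to confirm the efficacy of the CMOA in managing moderate OSA against MAD by monitoring" the seven measures before and after the intervention.
- The abstract (Methods) does announce a between-arm comparison: "The statistical significance between the two groups after one month and three months will be evaluated at" the 0.05 level. The abstract (Discussion) states the hypothesis that CMOA does better than MAD.
- The primary outcome is the change from baseline to 1 month.
- The Discussion says that ESS will be compared before and after intervention in order to analyse the efficacy of CMOA over MAD.
- Data management/handling with missing data says that continuous outcomes over time will be handled by a multi-level approach under a missing-at-random assumption, with pattern mixture models as sensitivity analyses. Statistical analysis does not mention this model.

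**The concern.** The trial's question is comparative, but a paired test within the CMOA arm says nothing about MAD. It also picks up whatever else changes between the two recordings. Patients enter on an AHI window (above 15 to 30), so regression to the mean can contribute to the before-after change; the document does not show in which direction. Two places, the closing sentence of Statistical analysis and the ESS paragraph of the Discussion, tie before-after monitoring to efficacy relative to MAD. Without a named decisive contrast, a report could present within-arm significance as the answer.

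The between-arm analysis is itself not settled. It is unclear whether the independent test is run on follow-up values (as the abstract's wording suggests) or on changes (as the primary outcome suggests). The normality result decides whether means or ranks are compared, so the quantity tested may differ between outcomes and visits. None of the listed tests uses baseline as a covariate, and none of them is the multi-level model that the missing-data section relies on.

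**Working it through.** **Inputs from the document.** Significance level 0.05, sidedness not stated (two-sided assumed). 20 per arm planned, with a minimum of 16 at 80% power (Study design). AHI falls of 12.7 and 13.8 events/h with monobloc and bibloc appliances (Discussion), used here as a stand-in for the MAD effect. No SD of change is given, so 6 to 15 is assumed.

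**The plan's own figure.** "At 80% power of the study, the minimum sample size calculated for each group is 16", but without an effect size or SD, so 16 cannot be reproduced forwards. Solving backwards with the normal formula, d = (1.960 + 0.842) × √(2/16) = 0.99. This describes what 16 implies and does not verify it.

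**Step 1: how often a half-as-good appliance passes a paired test.** Take a MAD fall of about 13 and a CMOA fall of 6.5. Paired test: noncentral t with n − 1 df and noncentrality (6.5/SD) × √n. At SD 8 and n=20: 0.8125 × 4.472 = 3.63, critical value 2.093, power 93%. Between-arm t-test of the same 6.5 difference: noncentrality (6.5/SD) × √(n/2) with 38 df. At SD 8: 0.8125 × 3.162 = 2.57, critical value 2.024, power 71%.

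| Assumed SD of change | Paired test significant in CMOA arm | Between-arm test shows CMOA worse | Between-arm test falsely shows CMOA better |
|---|---|---|---|
| 6 | over 99% | 92% | below 0.1% |
| 8 | 93% | 71% | below 0.1% |
| 10 | 79% | 52% | below 0.1% |
| 12 | 63% | 39% | below 0.1% |
| 15 | 45% | 27% | below 0.1% |

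Using exact halves of the two cited falls (6.35 and 6.9) moves the paired column by about 2 points down or 5 up. With 16 completers and SD 8, the paired figure for 6.5 is 86%.

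**Step 2: what baseline adjustment gains.** Change-score variance is SDb² + SDf² − 2r·SDb·SDf. ANCOVA variance is SDf²(1 − r²). The difference is (SDb − r·SDf)², which is never negative.

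- AHI, assuming baseline uniform over 15–30 (SDb = 15/√12 = 4.33) and SDf = 8. At r = 0.2: 68.9 against 61.4, ratio 1.12. At r = 0.4: 55.0 against 53.8, ratio 1.02. At r = 0.6: 41.2 against 41.0, ratio 1.005.
- Outcomes with equal SDs: ANCOVA variance over change-score variance is (1 − r²)/(2(1 − r)) = (1 + r)/2, that is 0.65, 0.75 and 0.85 at r = 0.3, 0.5 and 0.7.

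**Step 3: the normality gate.** The rule was simulated under no difference between arms, with 20 per arm, 10,000 runs, and a t-test only if both arms pass Shapiro-Wilk. The type I error was 5.1% for normal data, 5.6% for lognormal with sigma 0.5 and 4.8% for lognormal with sigma 1. The rule switched to Mann-Whitney in 10%, 76% and 99% of runs respectively. The error rate is hardly affected, but for moderately skewed data the sample decides which quantity is tested.

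**The case against.** The plan does contain valid between-arm tests: Statistical analysis names the independent t-test and Mann-Whitney, and the abstract announces the comparison between groups. The sentence about confirming efficacy expresses an expectation, says that it is relative to MAD, and sets no success rule. Regression to the mean acts on both randomised arms alike and cancels in their comparison. A change-score t-test in a randomised trial is unbiased, so ANCOVA is a gain in efficiency and corrects no error. Covariates and model form are often left to an analysis plan, which is not shown here.

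All of this stands, and it rules out several stronger readings that a reader might infer:

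- That an inferior appliance would be confirmed. No passage makes a paired test the criterion, and the listed between-arm t-test would call a half-as-good CMOA superior less than 0.1% of the time.
- That the plan is before-after only. It is not.
- That baseline data are thrown away. They enter by subtraction through the change score.
- That the Shapiro-Wilk gate inflates type I error. The simulation shows 4.8–5.6%.

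The objection does not remove the narrower point. The article states its tests, puts the before-after comparison first, does not say which test answers the trial's question, and describes a different analysis for continuous outcomes in another section.

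**Conclusion.** The point holds as a should-fix. The plan does not designate the between-arm contrast as the efficacy test, and it links before-after comparison to efficacy over MAD in two places. The chance that a half-as-good appliance shows a significant within-arm change runs from about 45% to over 99% at n=20. That figure assumes an SD of change between 15 and 6, two-sided 0.05, and the cited falls as the MAD effect. It measures how easily a within-arm result could mislead, not the chance of a false trial conclusion.

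The precision argument is modest for AHI: the change-score variance exceeds the ANCOVA variance by 0–12% (assumed baseline SD 4.3, follow-up SD 8, r 0.6 to 0.2). It is larger for outcomes whose SDs are equal at both visits, where adjustment removes 15–35% of the variance (r 0.7 to 0.3). The fault of the normality gate is that the quantity estimated is not fixed. The mismatch with the multi-level approach needs reconciling whatever SDs apply.

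**What to change.** In Statistical analysis:

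1. State that the between-arm difference (CMOA against MAD) at 1 month is the efficacy comparison.
2. For each continuous outcome, estimate it by ANCOVA with the baseline value, or by the mixed model that the missing-data section implies (arm, visit, arm-by-visit, baseline value). Report the adjusted difference with a 95% CI. With baseline in the model, follow-up values and changes give the same adjusted difference at a given visit, so that ambiguity disappears.
3. Fix the method in advance and drop Shapiro-Wilk as a selector. For outcomes expected to be skewed, such as ODI or time below 90% saturation, pre-specify a transformation or a rank-based sensitivity analysis.
4. Report within-arm changes descriptively, without p-values, and align the ESS sentence in the Discussion.

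The cost is wording and one degree of freedom (37 instead of 38 for an ANCOVA on all 40 patients), with no extra patients, visits or measurements. This does not cover ECG patterns, which are not a continuous outcome, and it does not reduce the seven measures under the primary outcome to one.
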